### Statistics

All analyses will be performed using SPSS Statistical Software (IBM SPSS Statistics for Windows, Version 21.0. Armonk, NY, USA). Continuous variables will be presented as mean ± SD, and categorical variables, as frequencies. Differences between the groups at baseline will be evaluated by an unpaired *t* test or the Mann–Whitney test for comparison of continuous variables. The Chi-square test or Fisher’s exact test will be employed to compare categorical variables. The change from baseline to 4-week follow-up in the groups will be evaluated using the paired *t* test for continuous variables. Pearson’s correlation will be used to assess the relation between BP reduction and treatment (intervention). For all analyses, a two-sided *P* < 0.05 will be considered statistically significant.

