Currently, nonpharmacological therapeutic methods are being used to treat RH. These are invasive, require long-term follow up to monitor the results and may cause unwanted complications during and after the procedure, besides being expensive. Examples of these methods are denervation or ablation of the renal sympathetic ganglia and chronic carotid baroreflex stimulation [48]. Both these techniques have generated good results in the reduction of peripheral BP by improving vasomotor tone related to sympathetic suppression; however, similar reductions in BP were reported for treatment and placebo groups [48, 49]. Thus, the identification of new noninvasive therapeutic approaches to control RH is essential. Transcutaneous electrical nerve stimulation (TENS) may be a new, easy to apply, reproducible, and inexpensive technique for this purpose. TENS is capable of inhibiting primary afferent pathways using low-frequency electrical pulses generated by electrodes attached to the skin, which cause local numbness and thus inhibit pain [50, 51]. In addition to the analgesic effects, electrical stimulation has been shown to enhance a local vasodilator effect, which may contribute to reducing BP and prevent ischemia [52]. Among the mechanisms that might explain this anti-ischemic action are the inhibition of sympathetic segmental vasoconstriction, release of vasodilatory peptides from sensory neurons, and the pump effect of muscle contractions [53–56]. Other favorable effects have been observed on applying TENS in the cervicothoracic ganglion region. The cervicothoracic ganglion or stellate ganglion, whose predominant action is sympathetic activity, is a confluence of nerves located in the posterior cervical region at the junction of the lower and upper thoracic cervical ganglia [53–58].

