### Sample size calculation

The site http://www.lee.dante.br/pesquisa/amostragem/amostra.html was used to estimate the sample size. The sample size calculation with a P alpha of 0.05, statistical power of 80 %, standard deviation of 8 mmHg, and maximum acceptable absolute difference of 6 mmHg (diastolic BP), indicated the necessity to study 28 patients per group (intervention versus sham). However, considering a potential 10–15 % dropout or loss to follow-up rate, 32 will be considered for each group. The difference of 5 mmHg (diastolic) has been achieved, on average, in clinical trials that have demonstrated the advantage of a drug over placebo or other nonpharmacological treatment in the prevention of major cardiovascular outcomes.

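### The test stated for the primary outcome is a paired t test within each arm; the only possible between-arm analysis is a Pearson correlation with undefined coding and no estimate in mmHg

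*Protocol article*

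**What the plan says.** The Protocol article's section on the primary outcome measure defines it as change from baseline in peripheral BP. The Design section describes a randomised, parallel-group, sham-controlled trial. The Sample size calculation section uses alpha 0.05, "statistical power of 80 %, standard deviation of 8 mmHg" and a diastolic difference of 6 mmHg, and arrives at 28 patients per group for TENS against sham, raised to 32 for dropout.

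The Statistics section then gives three instructions for continuous outcomes:

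- **Baseline:** "Differences between the groups at baseline will be evaluated by an unpaired" t test or a Mann–Whitney test.
- **Change to week 4:** "The change from baseline to 4-week follow-up in the groups will be evaluated using the paired" t test.
- **Association:** Pearson's "correlation will be used to assess the relation between BP reduction and treatment (intervention", closing bracket omitted here. How treatment is coded is not stated.

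Significance is two-sided at 0.05 throughout. For week-4 BP or its change, no unpaired test, regression model or TENS-minus-sham difference is named.

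**The concern.** The sentence that deals with the primary outcome names a test that cannot compare TENS with sham. A paired t test asks whether the mean change within one arm differs from zero. It attributes to stimulation everything that moves BP over four weeks: regression to the mean, repeated visits, attention and any sham effect.

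Some fall under sham is plausible here. The Ambulatory blood pressure monitoring section applies thresholds of raised BP to the patients considered, and Table 1 has both arms examined every week. The Background adds that, for two invasive sympathetic-suppression techniques, "similar reductions in BP were reported for treatment and placebo groups". That supports the worry by analogy only, since those are different interventions.

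At stake is the main conclusion. A significant fall in the TENS arm, or a significant fall with TENS and a non-significant one with sham, could be reported as efficacy although the arms do not differ. Conversely, if both arms fall significantly, a real advantage of TENS could go unseen.

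**Working it through.** **Inputs from the Protocol article.** Two-sided alpha 0.05 (Sample size calculation and Statistics); power 80%, SD 8 mmHg, difference 6 mmHg and 28 per group (Sample size calculation).

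**Assumption.** The article gives a "standard deviation of 8 mmHg" without saying whether it belongs to the change or to a single reading. The calculations below treat it as the SD of change unless stated otherwise.

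**1. Which comparison does the plan's 28 belong to?**

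- Two-sample formula: n per group = 2 × SD² × (1.960 + 0.842)² / difference² = 2 × 64 × 7.849 / 36 = 27.9, so 28. This reproduces the plan's figure. Power at 28 is 80.1% by the normal approximation and 78.7% by the noncentral t.
- One-sample (paired) formula with the same inputs: 64 × 7.849 / 36 = 13.95, so 14, or 16 using the t distribution.

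The trial is therefore sized for a comparison between two arms, which the sentence on change from baseline does not name.

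**2. What the paired test does when TENS has no effect.** Let both arms fall by the same mean amount m. With 28 per arm, the standard error of one arm's mean change is 8/√28 = 1.512 mmHg, the noncentrality is m/1.512 and there are 27 degrees of freedom. Write p for the probability that one arm's paired test is significant. The arms are independent, so TENS significant and sham not has probability p(1 − p).

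| Common fall m (mmHg) | TENS paired test significant, p | TENS significant, sham not, p(1 − p) |
|---|---|---|
| 2 | 25% | 19% |
| 3 | 48% | 25% |
| 4 | 72% | 20% |
| 5 | 89% | 10% |
| 6 | 97% | 3% |

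The last column cannot exceed 25%, which is the maximum of p(1 − p) and is reached near a 3 mmHg fall. A proper two-sided 0.05 comparison of the arms would wrongly favour TENS in 2.5% of such trials.

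**3. A true 6 mmHg advantage.** If sham falls by 4 mmHg and TENS by 10, the TENS paired test is almost always significant and the sham test is significant in 72% of trials. Both are then significant in about 72% of trials, a pattern that says nothing about the 6 mmHg difference.

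**4. The Pearson correlation.** If treatment is arm coded 0/1, this is a point-biserial correlation. In 2,000 simulated trials its p-value equalled that of the unpaired t test on change, to rounding error (largest difference about 1e-15). It reports r, however. For a 6 mmHg difference with SD 8 (standardised 0.75) and equal arms, r = 0.75/√(0.75² + 4) = 0.35, which does not convey the difference in mmHg or its confidence interval.

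**5. What a between-arm analysis would deliver.**

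- Unpaired t test on change, 28 per arm: standard error 8 × √(2/28) = 2.138 mmHg; 95% CI half-width 2.005 × 2.138 = 4.3 mmHg; power 78.7%, or 84.0% at 32 per arm.
- ANCOVA: variance relative to the change score is (1 + ρ)/2, where ρ is the baseline to week-4 correlation (assumed). ρ = 0.5 gives a working SD of 8 × √0.75 = 6.93 and power 89%; ρ = 0.7 gives 8 × √0.85 = 7.38 and power 85%.
- If 8 mmHg is instead the SD of a single reading, the SD of change is 8 × √(2(1 − ρ)). The change-score comparison then needs 40, 28 or 17 per group at ρ = 0.3, 0.5 or 0.7.

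**The case against.** The strongest reply is that a between-arm test is already there. If treatment in the Pearson sentence means randomised arm, that correlation is a valid two-sided comparison of change between TENS and sham, with the same p-value as an unpaired t test. This stands. A reader might infer from the paired test that the trial never compares TENS with sham and leaves the randomised question unanswered; the article does not support going that far. Nor does it show that the comparison is secured. The coding is not given, and the word could refer to something else, such as stimulation intensity, which the Application of TENS section adjusts to each patient. Even under the favourable reading there is no effect in mmHg, and the correlation is not the test attached to change from baseline.

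Four further points limit the argument:

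- The article states no rule that efficacy will be claimed when TENS is significant and sham is not. The table shows what such a reading would cost, not what the investigators have committed to.
- The 25% is a ceiling. At a common fall of 6 mmHg the figure is 3%.
- That BP will fall under sham is an inference, not something the article states.
- Baseline adjustment is an improvement, not the cure for an error. An unpaired t test on change would also answer the question.

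It might also be said that a condensed article leaves such matters to an analysis plan. That does not apply: the article does not leave the test open, it names one that does not fit the design.

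**Conclusion.** The point holds in a limited form, and it must be fixed because the main efficacy conclusion depends on it. The test attached to the primary outcome works within each arm, while the trial is randomised against sham and its 28 per group reproduces only as a two-sample number. Whether any stated analysis compares the arms depends on an undefined variable in a correlation, and none is stated to give a difference in mmHg with a confidence interval.

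Reliance on the paired tests could be seriously misleading. With no TENS effect, common falls of 2 to 6 mmHg make the TENS test significant in 25% to 97% of trials, and produce significance in TENS alone in 3% to 25%. These figures assume 28 analysed per arm, normally distributed changes, an SD of change of 8 mmHg and equal mean falls in both arms. The mismatch between test and design rests on the text alone and needs none of these assumptions.

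**What to change.** Name a between-arm comparison of BP as the primary analysis. The preferred form is an ANCOVA of week-4 BP on randomised arm with baseline BP as covariate. An unpaired t test on change is the minimum that matches the sample size calculation. Report TENS minus sham in mmHg with a 95% CI and a two-sided 0.05 test. Give within-arm changes as description only, and rest no efficacy conclusion on the paired tests or the correlation. If the correlation is kept, state how treatment is coded.

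The Trial status section says randomisation has begun, so this needs a dated amendment made before outcome data are examined. It requires no new measurements and no other software. No extra patients are needed if 8 mmHg is the SD of change, so the amendment should say which SD it is. Under that assumption ANCOVA would raise power at 28 per arm from about 79% to between 85% and 89%, for an assumed correlation between 0.7 and 0.5.

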### Randomization and follow‐up

#### Protocol

Patients will be divided into two groups: treatment and control (sham group). The sham group will be submitted to the procedure to fit the stimulation equipment. However, these patients will not be submitted to stimulation. Both groups will undergo a physical examination at the start and end of the study period to determine anthropometric variables. The BMI, defined as the weight (kg) divided by the patient’s height squared (m^2^), will be calculated. The height will be determined in centimeters using a measuring tape while the individual stands in bare feet. Individuals with a BMI < 25 kg/m^2^ will be classified as normal, overweight as a BMI between 25 and 30 kg/m^2^, and obese as a BMI ≥ 30 kg/m^2^. The waist circumference will be measured using a measuring tape at half the distance between the iliac crest and the lower costal margin. Patients will undergo the following tests before and after the end of the 4-week study period: 24-h ambulatory blood pressure monitoring (ABPM), 24-h dynamic electrocardiography, continuous measurement of beat-to-beat BP, endothelial function measurement (Endo-PAT 2000), and radial artery applanation tonometry (AT). Table 1 shows a summary of the key practical aspects of the study with all follow-up visits and requested exams, and Fig. 1 represents the flowchart of the study.

**Table 1 Tab1:** Key practical aspects of the study with all the clinical visits and the requested exams

Visits	Screening	1^st^ week	2^nd^ week	3^rd^ week	4^th^ week
Weeks	−1	1	2	3	4
Informed consent	X				
Inclusion and exclusion criteria	X	X			
Medical history	X				
Medical evaluation/physical examination (BP measure)	X	X	X	X	X
Randomization		X			
Application of TENS (3x/week)		X	X	X	X
Creatinine	X				X
Fasting glucose	X				X
Glycated hemoglobin	X				X
Potassium	X				X
Uric acid	X				X
Insulin	X				X
Total cholesterol	X				X
HDL-c	X				X
Triglycerides	X				X
Urinary sodium	X				X
Urinary potassium	X				X
Microalbuminuria	X				X
GFR estimation	X				X
Specific biochemistry tests		X			X
Ambulatory blood pressure monitoring		X			X
24-h electrocardiographic monitoring		X			X
Evaluation of sympathetic activity		X			X
Evaluation of endothelial function		X			X
Evaluation of arterial stiffness		X			X

*BP* Blood pressure, *TENS* transcutaneous electrical nerve stimulation, *HDL-c* high-density lipoprotein cholesterol, *GFR* glomerular filtration rate

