### Assessment of outcomes

Blood pressure (mean of two measurements by an automatic electronic device Omron HEM-711 DLX) and hemodynamic parameters (by Omron HEM 9000 AI device) will be measured in the office at the follow-up visits.

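### Office BP is taken weekly, but change is analysed by a two-time-point paired test that gives no baseline-adjusted TENS-minus-sham estimate; a cheap improvement is available

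*Protocol article*

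**What the plan says.** All places are in the protocol article.

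- **Statistics:** "The change from baseline to 4-week follow-up in the groups will be evaluated using the paired" t test. The section also plans a Pearson correlation between BP reduction and treatment. It names no repeated-measures method and no baseline-adjusted comparison of the arms.
- **Table 1:** the row "Medical evaluation/physical examination (BP measure)" is marked at screening and in weeks 1, 2, 3 and 4. Week 1 is also the week of randomisation and of the first TENS sessions.
- **Assessment of outcomes:** office BP and hemodynamic parameters "will be measured in the office at the follow-up visits". The weekly readings are therefore outcome data.
- **Sample size calculation:** 28 per group is raised to 32, "considering a potential 10–15 % dropout or loss to follow-up rate".
- **Missing or dropout:** only re-contact by phone or address is described.
- **Primary outcome measure:** change from baseline in peripheral BP, without saying whether this is office or ambulatory BP. Table 1 schedules ambulatory monitoring only in weeks 1 and 4.

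**The concern.** A paired t test within an arm asks whether BP fell in that arm. A sham-controlled trial needs the difference between arms, preferably adjusted for baseline, with a confidence interval in mmHg. The stated test also needs both values, so a patient seen in weeks 2 and 3 but not in week 4 contributes nothing, although those readings were taken.

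Two things are at stake. One is precision, because baseline adjustment costs nothing and is not planned. The other is bias: enrolling more patients replaces numbers, but it does not correct for losing a selected group. If patients leave because of their BP, and do so differently in the two arms, a completer-only comparison is distorted. A likelihood-based model that includes the weekly readings is not distorted, provided loss depends on BP values already observed.

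**Working it through.** **1. The plan's own figure.** Inputs from Sample size calculation: "The sample size calculation with a P alpha of 0.05", "statistical power of 80" percent, "standard deviation of 8 mmHg", difference 6 mmHg diastolic. The test is two-sided (Statistics: "For all analyses, a two-sided").

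n = 2 × SD² × (1.960 + 0.842)² / difference² = 2 × 64 × 7.85 / 36 = 27.9, so 28 per group. The stated figure reproduces.

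**2. Power after the expected loss.** Of 32 per group, 32 × 0.90 = 28.8 or 32 × 0.85 = 27.2 remain. Two-sample power for 6 mmHg at SD 8 is 81.2% and 79.0% by the normal approximation, or 79.9% and 77.5% by the t distribution. The planned 80% is roughly kept without any data from dropouts.

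**3. Baseline adjustment alone.** Let r be the correlation between baseline and week 4. The per-patient variance is 2 × SD² × (1 − r) for a change score and SD² × (1 − r²) for ANCOVA. Their ratio is (1 + r)/2. The article gives no correlations, so 0.5–0.7 is assumed.

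- Equal correlations: r = 0.5 gives 0.75 and r = 0.7 gives 0.85, a cut of 25% and 15%.
- Correlations decaying by week, with three weeks between weeks 1 and 4: r = 0.5³ = 0.125 gives 0.56 and r = 0.7³ = 0.343 gives 0.67, a cut of 44% and 33%.

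**4. What the extra visits add.** Generalised least squares variance of the week-4 difference: 32 per arm, 15% loss spread evenly over the intervals after week 1, a common baseline mean, week 1 as baseline. Power (normal approximation) takes 8 mmHg as the SD of change.

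| Assumed correlation | Extra variance cut beyond completer ANCOVA: weeks 2–3 | Same, plus screening | Power: change / ANCOVA / + weeks 2–3 / + screening |
|---|---|---|---|
| Equal, 0.5 | 1.5% | 11.9% | 79.0 / 89.1 / 89.6 / 92.5% |
| Equal, 0.7 | 2.2% | 17.9% | 79.0 / 85.1 / 85.8 / 91.2% |
| Decaying, 0.5 | 1.6% | 1.6% | 79.0 / 95.8 / 96.1 / 96.1% |
| Decaying, 0.7 | 3.0% | 3.0% | 79.0 / 92.2 / 92.9 / 92.9% |

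Over correlations of 0.5–0.9 and loss of 10–15%, weeks 2 and 3 add 1.0–4.6%. Under decay, screening adds nothing.

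**5. Bias, by a constructed example.** True effect 6.0 mmHg, SD 8, equal correlations of 0.6. The 15% of sham patients with the largest rise by week 3 leave; loss on TENS is random.

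- The SD of the week-3 change is 8 × √(2 × 0.4) = 7.16. Removing the top 15% shifts its mean by −0.233/0.85 = −0.274 SD.
- The covariance of the week-3 and week-4 changes is 64 × 0.4 = 25.6. The week-4 change in sham therefore shifts by −0.274 × 25.6/7.16 = −0.98, and the completer change-score estimate is 6.0 − 0.98 = 5.0.
- Simulation with 400,000 per arm gives 5.0 for completer change, 5.4 for completer ANCOVA and 6.0 for the likelihood model with all visits. With decaying correlations the figures are 4.0, 4.9 and 6.0.
- If the same rule removes patients from both arms, the two completer estimates return to 6.0. With a graded sham-only rule (log-odds of leaving rising 0.1 per mmHg, equal correlations) they are about 5.6 and 5.8.

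**The case against.** - **A single week-4 endpoint analysed at two time points is conventional, and missing-data rules are often left to an analysis plan, which is not shown.** This stands in part. That dropouts are excluded is inferred from the test; the article does not say it, and a missing-data rule may exist elsewhere. But the article does fix the test, and that choice can be judged.
- **The dropouts are already paid for.** This stands. A reader might infer that losing 10–15% leaves the trial underpowered; step 2 shows otherwise.
- **The power gain does not belong to the weekly visits.** This stands. A reader might credit the unused visits with lifting power from about 78% to around 90%. Step 4 shows that baseline adjustment does most of this. The only other sizeable part comes from the screening reading, and only when correlations do not decay.
- **The comparator is not the stated test.** This stands as a caution. The figures compare with a between-arm test of change, while Statistics states a paired test in the groups. If treatment in the planned Pearson correlation means arm, its P value equals that of a two-sample t test of change. It still gives no difference in mmHg and no baseline adjustment.
- **The bias example is extreme.** This stands. Nothing in the article shows that loss will differ by arm. Design calls the trial open-label, but the abstract calls it single blind (subject), and sham patients are fitted with the equipment. That contradiction is not evidence of selective dropout.
- **Primary BP may be ambulatory.** This stands. There would then be no weekly values for the primary outcome.

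**Conclusion.** The point holds as a cheap improvement. The stated test uses two time points, depends on having both values, and does not deliver a baseline-adjusted TENS-minus-sham estimate, although office BP is collected at screening and in weeks 1 to 4.

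Against a change-score comparison, most of the precision gain comes from baseline adjustment (15–44% of the variance at assumed correlations of 0.5–0.7). The intermediate visits add roughly 1–5% beyond completer ANCOVA, and a second baseline takes the total to about 12–18% only with non-decaying correlations. The stronger reason for using the weekly readings is protection against bias, and that needs loss to depend on observed BP and to differ by arm. The documents support neither a claim that the trial loses its planned power nor one that its estimate will be biased by a given amount. The power figures also assume that 8 mmHg is the SD of change, which the article does not state.

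**What to change.** - **Office BP:** replace the paired test with a mixed model for repeated measures in all randomised patients, with arm, week and arm-by-week terms and an unstructured covariance. Use the screening and pre-first-session readings as baseline and the later weekly values as outcomes. Report the week-4 TENS-minus-sham difference in mmHg with its 95% CI.
- **Outcomes measured only twice (ambulatory BP, tonometry as scheduled in Table 1):** use ANCOVA adjusted for the baseline value.
- **Definitions:** say whether primary peripheral BP is office or ambulatory, and whether the week-1 office reading precedes the first session. If primary BP is ambulatory, only the ANCOVA part applies to it.

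The cost is wording. No new visits or data are needed, and the named SPSS package fits linear mixed models. The downside is a slightly more complex model with little precision gain over ANCOVA if correlations decay. Since Trial status says that randomisation has begun, the change should be dated and fixed before any outcome is compared by arm.

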### Research question

The following research questions will be explored:Does TENS constitute a new therapeutic option in the reduction of peripheral blood pressure of patients with resistant hypertension?Does TENS constitute a new therapeutic option in the reduction of central pressure of resistant hypertensive patients?Does TENS reduce arterial stiffness measurement parameters?Can TENS positively influence metabolic disorders that involve the progression of arterial stiffness?

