### General biochemistry assessment

Biochemical tests will be performed at two time points, before and after the 4-week study period, and include blood sugar, glycated hemoglobin, total cholesterol (TC), high-density lipoprotein cholesterol (HDL-C), triglycerides (TG), creatinine, potassium, uric acid, and plasma insulin levels.

Blood sugar, TC, HDL-C, and TG levels will be determined by colorimetry after fasting for 12 h using a RXL Dimension device with the Dade Behring reagent. Diagnosis of diabetes mellitus (DM) will be established by patient history, the use of hypoglycemic drugs, and measurement of the serum glucose [68]. The LDL-C fraction will be calculated using the formula LDL-C = TC - HDL-C - TG/5 (for TG < 400 mg/dL) [69]. Additionally, the electrochemiluminescence method will be used to measure plasma insulin (immunoassay for the in vitro quantitative determination of human insulin in serum and plasma using the Elecsys 1010/2010 immunoassay and E170 modular analytics analyzers by Roche). The homeostasis model assessment of insulin resistance (HOMA-IR) index will be applied after obtaining blood sugar and insulin levels in order to determine insulin resistance and the functional capability of the pancreatic beta cells. Insulin resistance will be characterized when this ratio exceeds 2.71 [70]. The HOMA-IR index is calculated using the following formula:$$ \mathrm{HOMA}\hbox{-} \mathrm{I}\mathrm{R}:\;\frac{\mathrm{Fasting}\;\mathrm{insulin}\left(\mathrm{M}\mathrm{c}\mathrm{U}/\mathrm{mL}\right)\times \mathrm{fasting}\;\mathrm{glucose}\left(\mathrm{mmol}/\mathrm{L}*\right)}{22.5}. $$

In order to convert the glucose concentration to mmol/L it is necessary to multiply the value in mg/dL by 0.0555.

Measurement of serum creatinine will be performed by a standardized enzyme-kinetic biochemical test and will be considered high when serum creatinine is > 1.4 mg/dL [71, 72].

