### Specific biochemistry tests

Specific biochemical tests will be considered (Table 2): serum aldosterone (AS); plasma renin activity (PRA); highly sensitive C-reactive protein (hsCRP); metalloproteinase 9 (MMP-9); tissue inhibitors of metalloproteinase (TIMP-1 and TIMP-2); nitrites and nitrates; interleukin-1, 6, 8, 10, and 18 (IL-1, IL-6, IL-8, IL-10 and IL-18); TNF-α, thromboxane B_2_ (TXB_2_); fibrinogen; intercellular adhesion molecule-1 (ICAM-1); plasminogen activator inhibitor (PAI-1); angiotensin converting enzyme (ACE); and angiotensin II (Ang II).

**Table 2 Tab2:** Specific biochemistry tests

Inflammatory markers and endothelial dysfunction	
• IL-1, IL-6, IL-8, IL-18 • TNF-α • hsCRP and fibrinogen • intercellular adhesion molecule (ICAM-1)	
Anti-inflammatory	
• IL-10	
Coagulation	
• plasminogen activator inhibitor (PAI-1) • fibrinogen	
Renin Angiotensin Aldosterone System	
• Ang II • angiotensin converting enzyme (ACE) • plasma renin activity • serum aldosterone	
Extracellular matrix and tissue inhibitors	
• MMP-9 • TIMPs	

*IL* interleukin, *Ang II* Angiotensin II, *TNF-α* tumor necrosis factor alpha, *hsCRP* highly sensitive C-reactive protein, *MMP* metalloproteinase, *TIMPs* tissue inhibitors of metalloproteinase

To evaluate the hsCRP, MMP-9, TNF-α, AS, PRA, TIMPs-1 and −2, nitrites and nitrates, IL-1, IL-6, IL-8, IL-10, IL-18, thromboxane B2, and fibrinogen levels, plasma samples will be obtained after centrifugation at 3500 rpm and 4 °C for 15 min immediately after collection and then stored at −80 °C for later analysis. The IL-1, IL-6, IL-8, IL-10, IL-18, TNF-α, MMP-2 and −9, ACE, and Ang II will be measured using the ELISA technique (R & D systems, Minneapolis, MN, USA) according to the manufacturer’s instructions and as described in a previous study [75]. The hsCRP is determined by a highly sensitive assay with a BN II nephelometer (Dade Behring, Marburg, Germany). The multiplex method will be used to measure the PAI-1 and ICAM-1 inflammatory mediators [14]. Plasma concentrations of tissue inhibitors (TIMP-1 and −2) will be measured using a commercially available enzyme-linked immunosorbent assay (R & D Systems, Minneapolis, MN, USA) according to the manufacturer’s instructions.

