### Adverse events

The adverse events will be investigated by open questions and by a semistructured questionnaire, which will address general symptoms and the presumed adverse effects of the electrostimulation used in the trial. Laboratory adverse events, such as metabolic changes and inflammatory markers, will be investigated at the final visit of the participants.

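### One unadjusted two-sided 0.05, applied to within-group change, covers about 34 laboratory markers that are neither primary nor secondary outcomes, so a chance finding in the TENS arm is likely unless the markers are labelled exploratory

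*Protocol article*

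**What the plan says.** The Statistics section of the protocol article gives one significance rule with universal scope. It opens "For all analyses, a two-sided" and ends "0.05 will be considered statistically significant". No adjustment, order of testing or exception for laboratory values goes with it. The test of change is also fixed: "The change from baseline to 4-week follow-up in the groups will be evaluated using the paired *t* test for continuous variables".

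The laboratory programme is wide. General biochemistry assessment lists nine blood tests, ending with "creatinine, potassium, uric acid, and plasma insulin levels", and adds two calculated indices: LDL-C ("The LDL-C fraction will be calculated using the formula") and HOMA-IR. Table 1 adds four urinary or renal measures. Specific biochemistry tests then names 19 further markers.

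The use of these values is left open. One research question reads "Can TENS positively influence metabolic disorders that involve the progression of arterial stiffness" and singles out no marker. The matching objective is only to observe biochemical and inflammatory changes. The primary outcome is peripheral blood pressure, and the secondary outcomes are arterial stiffness parameters including central pressure, so the laboratory markers belong to neither. The Adverse events section gives them a safety role as well: "Laboratory adverse events, such as metabolic changes and inflammatory markers, will be investigated at the final visit of the participants".

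**The concern.** The rule gives a cytokine or a lipid the same threshold, and the same word for passing it, as the primary outcome. With about 34 such variables and a question that any one of them could seem to answer, some will probably cross 0.05 by chance. Under the stated rule that marker would be reported as significantly changed after TENS, and could be read as support for a metabolic benefit. Chance changes in the unfavourable direction matter too, because the same variables are read as laboratory adverse events.

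The choice of test adds to this. A paired test inside the TENS arm cannot separate an effect of stimulation from a time trend, a response to the sham procedure that would occur in either arm, or regression to the mean.

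**Working it through.** The article gives no error rate for the laboratory set, so there is no figure of its own to reproduce.

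**Step 1: count the markers.**

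- Table 1, general tests: creatinine, fasting glucose, glycated hemoglobin, potassium, uric acid, insulin, total cholesterol, HDL-C, triglycerides, urinary sodium, urinary potassium, microalbuminuria, estimated GFR = 13.
- Derived in General biochemistry assessment: LDL-C, HOMA-IR = 2.
- Specific biochemistry tests: aldosterone, renin activity, hsCRP, MMP-9, TIMP-1, TIMP-2, nitrites and nitrates, IL-1, IL-6, IL-8, IL-10, IL-18, TNF-α, thromboxane B2, fibrinogen, ICAM-1, PAI-1, ACE, angiotensin II = 19. Fibrinogen stands twice in Table 2 and is counted once.

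Total: 13 + 2 + 19 = 34. MMP-2 appears only in the assay text; counting it gives 35.

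**Step 2: independent tests in the TENS arm, no true change.** With m markers, the chance of at least one P < 0.05 in either direction is 1 − 0.95^m, with 0.05m expected. A false improvement uses only the favourable tail, so its chance is 1 − 0.975^m, with 0.025m expected.

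| Set | Either direction | Expected | Improvement only | Expected |
|---|---|---|---|---|
| 34 markers | 1 − 0.95^34 = 82.5% | 1.7 | 1 − 0.975^34 = 57.7% | 0.85 |
| 35 (with MMP-2) | 83.4% | 1.75 | 58.8% | 0.875 |
| 19 specific only | 62.3% | 0.95 | 38.2% | 0.475 |

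**Step 3: correlated markers.** The documents give no correlations, so a common correlation is assumed and varied. Results for m = 34 come from 100,000 simulated sets of equicorrelated normal test statistics. At zero correlation the simulation gives 82.3% and 57.6%, in line with Step 2.

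| Assumed correlation | Either direction | Improvement only |
|---|---|---|
| 0.1 | 80% | 50% |
| 0.3 | 70% | 37% |
| 0.5 | 53% | 27% |
| 0.7 | 36% | 18% |

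Some dependence is certain: GFR is computed from creatinine, LDL-C from the other lipids, and HOMA-IR from glucose and insulin. The Step 2 figures are therefore upper limits for chance error alone.

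**Step 4: what these figures leave out.** They assume that mean change within the TENS arm is zero when TENS does nothing. A time effect, a sham-type response or regression to the mean would break that assumption and could raise the rate. The documents give nothing with which to size this.

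**The case against.** A reader might infer that a false claim of benefit is close to certain. The figures do not support that. The 83% counts worsening as well as improvement, and the improvement-only ceiling is about 58%. To reach 95% would take ln 0.05 / ln 0.95 = 58.4, so 59 independent tests in either direction, or ln 0.05 / ln 0.975 = 118.3, so 119 for improvement. A reader might also expect a handful of spurious markers. Testing both arms does give 68 × 0.05 = 3.4 expected, but half of those tests are in the sham arm, where a change cannot support a TENS benefit. In the TENS arm, less than one false improvement is expected.

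The article also does not say that all 34 values will be tested to answer the metabolic question. That is inferred from the words covering all analyses and from the generic method for continuous variables. Several values also serve safety, and glycated hemoglobin serves eligibility.

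The strongest defence is that the markers already rank below the primary and secondary outcomes, with an objective only to observe them. Strict error control is not usual for such measures, and an analysis plan that is not shown may deal with them. Much of this stands, and it is why the point is minor. It does not remove the point, because the article states a rule instead of leaving a gap. The rule exempts nothing, the markers are never called exploratory, and a later plan would have to override the sentence.

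The improvement-only figure also presumes that the favourable direction of each marker was fixed beforehand. The Statistics section fixes none, and for the TIMPs the Background speaks only of a balance with the MMPs. Where direction is settled afterwards, the chance moves from 58% towards 83%.

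**Conclusion.** The point holds as a minor improvement to the analysis rule. About 34 laboratory markers outside the primary and secondary outcomes share an unadjusted two-sided 0.05, tested as within-group change, behind a question that names no key marker. With no true change, a chance finding in the TENS arm is likely: up to about 83% for any marker and up to about 58% for an apparent improvement. A moderate correlation of 0.3 to 0.5 would bring these to about 70–53% and 37–27%.

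This rests on three assumptions: that every listed marker is tested, that the null is zero mean change within the arm, and that correlation has the simple form used above. It does not touch the primary blood pressure analysis, and it does not show that a false metabolic claim is inevitable.

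**What to change.** Three changes to the Statistics section:

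1. State that the general and specific laboratory markers are exploratory, and that the two-sided 0.05 rule does not by itself support a claim that TENS changed any of them.
2. For each marker, report the TENS-versus-sham difference in change from baseline with a 95% confidence interval, in place of reliance on within-arm paired tests. This removes changes common to both arms. It does not reduce the number of tests, which is why the third change is needed.
3. Before stating that TENS changed any of the 19 specific markers, apply the Benjamini-Hochberg procedure at a 5% false discovery rate to their between-arm tests. The kth smallest of the 19 P values is compared with k × 0.05/19, which starts at 0.05/19 = 0.0026. The 15 general and derived markers are reported as estimates with intervals only.

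The cost is wording alone, with no new data, visits or participants. Randomization has begun, but the change can still be made before analysis. The downside is that fewer markers can be called significant, and a real change in a single marker may go unclaimed.
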